### Methods for additional analyses (e.g., subgroup analyses) {20b}

A cost-utility analysis (CUA) will be performed to compare financial aspects of FCA and PRC. The cost per quality-adjusted life year (QALY) method is used to compare the cost-utility ratio of FCA and PRC. The quality of health will be followed with EQ-5D-5L index and the change in this index at 1 year after surgery will be multiplied by the number of years spent in that health state to determine the number of QALYs gained or lost. To estimate QALYs gained or lost during patients’ lifetime, we will multiply the change in EQ-5D-5L index with the expected life years remaining. We will use the data from Official Statistics of Finland [32] to determine the life expectancy for each patient. We will use a constant discount rate of 5% when calculating the total QALYs gained over lifetime to account for a projected diminishing gain over time [33]. To calculate cost of QALY, we will divide the total expenses of FCA and PRC with the change of EQ-5D-5L. This will be adjusted to give the cost per QALY over the course of lifetime.

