Although several studies report the outcomes of PRC and FCA, there is a paucity of high-quality evidence that would support the use of one technique over another. Two RCTs exist comparing these techniques [6, 7]. However, these trials suffer from methodological shortcomings, such as lack of blinding, high risk of selection bias, and incomplete outcome reporting. Generally, studies show no significant difference in ROM, grip strength, pain, or patient-rated outcomes [6–8]. However, some study groups suggest that FCA may be superior in terms of grip strength, while PRC may be preferable in terms of ROM, postoperative complications, and secondary operations [9–12]. Some studies indicate that PRC is more cost-effective [13, 14], while Daar et al. [15] concluded that FCA with cannulated compression screws is the most cost-effective approach. A long-term study reported fewer arthritic changes after FCA versus PRC. However, there was no apparent correlation between radiographic OA and patient satisfaction [16].

The most recent meta-analysis comparing PRC and FCA from Kamir et al. (2020) used flexion/extension ROM, grip strength, and pain level as outcome measures. They found that PRC was statistically but not clinically significantly better than FCA in all outcome measures [17].

Wrist OA due SLAC- and SNAC-degenerative pattern remains a common disorder encountered by a wrist surgeon. To date, most surgeons will choose to manage patients with SLAC/SNAC OA with FCA over PRC. However, the use of PRC has gained popularity among clinicians due its simplicity and predictable results, without the need to remove hardware or control for bony union. We hypothesize that PRC is non-inferior to FCA with lower economic expanses. While superiority of either procedure may be insurmountable to present, a thorough assessment of important considerations, such as AEs, postoperative pain, ROM, and convalescence time, should be examined by means of a randomized controlled trial (RCT). Thus, we planned a study protocol for a multicenter, double-blinded, randomized controlled non-inferiority trial comparing PRC vs FCA for the treatment of SLAC/SNAC I-II OA of the wrist.

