### Rehabilitation

All participants will undergo an identical standardized postoperative rehabilitation for the first 12 postoperative weeks. The short arm splint applied in the operative theater and stitches will be removed 3 weeks postoperatively. Thereafter, the participants will perform active ROM exercises 3–5 times a day. A short arm removeable splint will be used until 6 weeks after the procedure. From 6 weeks onwards, the participants will perform active and passive ROM exercises and will be allowed to use the hand as tolerated. A physio- and/or occupational therapist specialized in treating hand surgery outpatients will instruct the participants at 3 and 6 weeks after the operation. After 12 weeks, any other rehabilitation input beyond the protocol will be at the discretion of the RIs.

Patient rehabilitation will be followed by RIs at an outpatient clinic. Both the patient and RI will be blinded to the allocation until 12 months post-surgery. Outcome measures collected during follow-up are presented in the “Outcomes {12}” section.

Cone beam computed tomography (CBCT) will be performed alongside the clinical follow-up at 6 and 12 weeks and 6 and 12 months after study procedure. To maintain blinding, the CBCT will be screened by the surgeon who will give permission to continue according to the rehabilitation program if no adverse events occur that would compromise the rehabilitation program. Neither RIs nor patients will have access to CBCT imagining before the primary endpoint of the study has been reached at 12 months. Long-term follow-up will include standard PA and lateral X-rays at 5 and 10 years after the surgery.

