### Participant timeline

Follow-up will take place at 3 and 6 weeks, at 3, 6, and 12 months, and at 5 and 10 years post-treatment. The trial schedule of enrollment, interventions, assessments, and data collection are presented in Table 4.

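### The cost-utility analysis builds QALYs from the 1-year EQ-5D-5L change alone, so the course of recovery during year 1 gets no weight on the QALY side

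*Protocol article*

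**What the plan says.** All of the QALY rule stands in the protocol article, Methods for additional analyses {20b}:

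- Trial horizon: "the change in this index at 1 year after surgery will be multiplied by the number of years spent in that health state".
- Lifetime horizon: "we will multiply the change in EQ-5D-5L index with the expected life years remaining".
- Discounting: "We will use a constant discount rate of 5% when calculating the total QALYs gained over lifetime". The reason given is an expected decline of the gain over time.
- Cost per QALY: "we will divide the total expenses of FCA and PRC with the change of EQ-5D-5L", then adjusted to a lifetime figure.

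The same section says "The quality of health will be followed with EQ-5D-5L index", but only the 1-year change appears in the formula.

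Elsewhere in the article:

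- Participant timeline: "Follow-up will take place at 3 and 6 weeks, at 3, 6, and 12 months, and at 5 and 10 years post-treatment". Table 4, which would show the visits that include EQ-5D-5L, is not reproduced in the text at hand.
- Rehabilitation: "A short arm removeable splint will be used until 6 weeks after the procedure". This applies to both arms.
- EQ-5D-5L and cost-utility analysis: complications and sick leave are included in the costs.
- Background and rationale {6a}: considerations "such as AEs, postoperative pain, ROM, and convalescence time, should be examined" in a randomized trial.

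**The concern.** A QALY total is utility accumulated over time, that is, the area under the utility curve. The stated rule replaces the year-1 curve with a rectangle whose height is the 12-month change. During splinting and rehabilitation a patient is unlikely to be at the 12-month level already.

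Two things follow:

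1. **Level.** If the duration includes year 1, a patient who improves gradually is credited with more QALYs in that year than were lived. The 1-year cost per QALY then looks too favourable.
2. **Comparison.** Equal 12-month changes give equal QALYs. A complication that has resolved by month 12 raises an arm's cost and leaves its QALYs untouched. Non-union can occur only after FCA, so the omission need not cancel between arms.

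Cost-effectiveness is among the trial's objectives, and lower cost with PRC is part of its hypothesis. The 1-year cost-utility result is therefore a planned conclusion in its own right.

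**Working it through.** The article gives no QALY figure, so there is none to reproduce. The check compares the stated rule with the area under the curve.

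**Inputs from the article:** visits at 0, 3 and 6 weeks and at 3, 6 and 12 months; discount rate 5%. **Assumed, because the article gives no EQ-5D-5L values:** a 12-month gain G = 0.15 in each arm, EQ-5D-5L available at every visit, and the recovery paths below.

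**Year 1.** Stated rule: G × 1 = 0.150 for any path. Area: sum over intervals of (g_i + g_(i+1))/2 × (t_(i+1) − t_i), where g is the gain over baseline and t = 0, 3/52, 6/52, 0.25, 0.5, 1.

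| Assumed path (gain at 3 wk, 6 wk, 3, 6, 12 mo) | Area | Area ÷ 0.150 |
|---|---|---|
| Linear rise | 0.075 | 0.50 |
| Fast: −0.05, 0.05, 0.12, 0.15, 0.15 | 0.119 | 0.79 |
| Slow: −0.10, −0.05, 0.03, 0.09, 0.15 | 0.066 | 0.44 |
| Slow, deep dip: −0.20, −0.15, −0.05, 0.05, 0.15 | 0.021 | 0.14 |

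For the linear rise the ratio is 0.5 for any G, so the over-credit is a factor of 2.

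**Between arms.** With one arm fast and the other slow, the year-1 difference is 0.119 − 0.066 = 0.052 from unrounded areas (0.1187 − 0.0664 = 0.0523). It is 0.098 if the slower arm has the deep dip. The stated rule gives 0 in both cases. A second illustration assumes indices at 0, 3, 6 and 12 months of 0.65/0.80/0.85/0.85 and 0.65/0.65/0.75/0.85:

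- first arm: 0.075 × 0.25 + 0.175 × 0.25 + 0.20 × 0.5 = 0.1625
- second arm: 0 × 0.25 + 0.05 × 0.25 + 0.15 × 0.5 = 0.0875
- difference 0.075, against 0.20 − 0.20 = 0 under the stated rule.

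**Lifetime.** Discounted years A = sum of 1/1.05^y for y = 0 to L − 1, with L the remaining years. Stated figure: G × A. Corrected figure: G × (A − 1) + year-1 area. Over-credit as a share of the stated figure: (G − area)/(G × A).

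| L | A | Stated | Over-credit: fast | linear | slow | deep dip |
|---|---|---|---|---|---|---|
| 10 | 8.11 | 1.216 | 2.6% | 6.2% | 6.9% | 10.6% |
| 20 | 13.09 | 1.963 | 1.6% | 3.8% | 4.3% | 6.6% |
| 40 | 18.02 | 2.703 | 1.2% | 2.8% | 3.1% | 4.8% |

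**If the duration starts at month 12 instead.** Year 1 then carries no QALYs. With L = 10 the lifetime figure is 0.15 × (8.11 − 1) = 1.066, below all the corrected figures (1.087 to 1.185). The error reverses direction, and recovery still gets no weight.

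**The case against.** A reader might infer more than the documents support.

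- **That the article credits full benefit from the day of surgery.** It does not say so; the start of the duration is not stated. Inclusion of year 1 is an inference. It is a fair one, because costs are divided by the bare change (which amounts to one full year at the 12-month level) and because nothing is deducted from remaining life for recovery.
- **That year-1 QALYs are necessarily overstated in both arms.** This depends on the path. It can fail if utility peaks before 12 months, or if the 12-month change is zero or negative, which the article allows for. If both arms follow the same proportional path, the year-1 error scales both alike and leaves their QALY ranking unchanged.
- **That the plan hides a real difference of 0.05 to 0.10 QALY.** Those figures come from assumed indices. Rehabilitation is identical in both arms for 12 weeks, so the splint is no evidence that recovery differs.
- **That recovery is ignored altogether.** Sick leave and complications enter the costs, and continuous outcomes are analysed with a group-by-time term. The gap is confined to the QALY term.
- **That the 5% discount is an error.** Discounting lifetime QALYs is ordinary practice. Only the reason given is wrong: discounting expresses time preference and does not model a waning effect. Rewording it changes no number.

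Two further objections stand in part. The cost-utility ratio is finally expressed over a lifetime, where the effect is modest. And the benefit of the fix depends on EQ-5D-5L having been collected between baseline and 12 months, which cannot be checked here; the Outcomes section names EQ-5D-5L among outcomes at the 1-year follow-up.

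None of this removes the core point. The article states a formula, so this is not a detail left to a fuller plan, and that formula uses one change score only.

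**Conclusion.** The concern holds for the QALY term. Equal 12-month changes over equal durations give equal QALYs whatever the course of year 1, and this needs no assumption about utilities or about when the duration starts.

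The over-credit in year 1 is conditional on the duration including that year and on gradual improvement. It is a factor of 2 for a linear rise; on the other assumed paths the true credit is 14% to 79% of the stated one. On an arm's lifetime figure the over-credit is about 1% to 11% with 10 to 40 years remaining, on the same assumed paths. The size of any missed between-arm difference is unknown.

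The point matters for the 1-year cost-utility result, less for the lifetime result, and not for the primary PRWE non-inferiority conclusion. It should be corrected, but it does not threaten the trial.

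**What to change.** Reword the cost-utility paragraph in {20b}:

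1. Compute year-1 QALYs per patient as the trapezoidal area under the EQ-5D-5L index over all visits at which it is collected up to 12 months.
2. Compare arms adjusted for baseline index.
3. Use these QALYs, or the incremental QALYs between arms, as the denominator of the 1-year cost-utility result in place of the bare change.
4. In the discounted lifetime projection, apply the 12-month value only from month 12 onward. Describe the projection as assuming a constant gain, and do not present discounting as a model of waning.
5. If EQ-5D-5L exists only at baseline and 12 months, use linear interpolation. State as a limitation that it corrects the over-credit but cannot show recovery differences.

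The cost is analysis wording and a little programming. No added patients or visits are needed, since the rule uses whatever EQ-5D-5L visits the trial has. The change is best made before any unblinded analysis.

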### EQ-5D-5L and cost-utility analysis

EQ-5D-5L is a standardized measure of health status developed by the EuroQol Group to provide a simple, generic measure of health for clinical and economic appraisal. Applicable to a wide range of health conditions and treatments, it provides a simple descriptive profile and a single index value for health status that can be used in the clinical and economic evaluation of health care. EQ-5D is designed for self-completion by respondents. It is cognitively undemanding and takes only a few minutes to complete [30]. In addition to health state evaluation, EQ-5D-5L will be used for the cost per quality-adjusted life year (QALY) gained evaluation after the procedure.

The costs will include treatment costs and possible costs of complications and sick leave. The costs of treatments and complications will be analyzed by collecting the actual use of healthcare services and multiplying the use of service by unit costs. Sick leaves and their societal costs will be collected from Social Insurance Institution of Finland (KELA).

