### Sample size {14}

The primary outcome measure is PRWE and the primary hypothesis of our trial is that PRC is non-inferior to FCA in the treatment of SLAC/SNAC OA I-II measured with PRWE total score. The non-inferiority margin is set at 11.5 points using the PRWE minimally clinically important difference [31]. To exclude the non-inferiority margin, the trial will require 37 patients in each group to observe MCID (non-inferiority margin 11.5, SD 14) in PRWE scores between the trial groups with a power of 90% and using a one-sided type I error rate of 2.5%. We will recruit 84 patients to account for 10% loss during follow-up.

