## Assignment of interventions: allocation

### Sequence generation {16a}

A randomization sequence will be generated using an internet-based program (sealedenvelope.com). Patients will be allocated to one of the two treatment groups in a 1:1 ratio using permuted block randomization with variable block size.

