## Statistical methods

### Statistical methods for primary and secondary outcomes {20a}

Statistical analysis will be performed with both per-protocol and intention-to-treat (ITT) methods, the latter being the primary analysis. Descriptive statistics will be presented as mean (standard deviation) or median (interquartile range) for continuous variables and count (percent) for categorical variables.

For the continuous outcomes, we will compare the groups using a mixed model for repeated measurements (MMRM) entering group, group*time interaction as fixed factors, study site as a random factor, and baseline value as a covariate to the model. Marginal effects with 95% confidence intervals from the model will be reported as treatment effects. For the global improvement, we will use ordinal logistic model.

Statistical significance is set at 0.05. As comparisons of secondary outcomes are considered hypothesis generating, we will not adjust for multiple comparisons.

A statistical software program will be used for analyzing entered data. Blinded data interpretation will be used to reduce interpretation bias; therefore, the biostatistician will be unaware of the group assignments when performing the analyses.

The criterion for statistical significance will be set at *p* = 0.025 (one-sided) or *p* = 0.05 (two-sided). All *p*-values will be reported to three decimal places, with those less than 0.001 reported as *p* < 0.001.

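### QALYs and cost per QALY are built from each arm's EQ-5D-5L change without baseline adjustment, although the trial's model for continuous outcomes adjusts for baseline

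*Protocol article*

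**What the plan says.** The protocol article gives EQ-5D-5L two uses. It is a listed secondary outcome (Table 1 and Outcomes, 12), and the section on EQ-5D-5L and cost-utility analysis adds: "In addition to health state evaluation, EQ-5D-5L will be used for the cost per quality-adjusted life year (QALY) gained evaluation after the procedure".

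For continuous outcomes, Statistical methods for primary and secondary outcomes (20a) specifies a mixed model for repeated measurements with "study site as a random factor, and baseline value as a covariate to the model".

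For QALYs, Methods for additional analyses (20b) writes out its own rule in four steps:

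- One-year QALYs: "the change in this index at 1 year after surgery will be multiplied by the number of years spent in that health state".
- Lifetime QALYs: "we will multiply the change in EQ-5D-5L index with the expected life years remaining", with life expectancy taken from national statistics for each patient.
- Discounting: "We will use a constant discount rate of 5% when calculating the total QALYs gained over lifetime".
- Cost per QALY: "we will divide the total expenses of FCA and PRC with the change of EQ-5D-5L".

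None of these steps names a baseline covariate. The only adjustment mentioned in that paragraph is the rescaling of the cost ratio to a lifetime.

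**The concern.** A change score subtracts the whole baseline value. The 1-year value usually follows baseline with a slope below 1, so this subtracts too much. If one arm happens to start with a lower EQ-5D-5L, its mean change tends to be larger even when the two operations are equally good. A model with baseline as a covariate removes only the part that baseline predicts, so it does not have this problem.

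At stake is the comparison of PRC and FCA on QALYs and on cost per QALY. If the paragraph is followed as written, part of any chance imbalance counts as health gained, is projected over a lifetime, and enters the denominator of each arm's cost ratio. The estimate is also noisier than one the trial can obtain from the same data.

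**Working it through.** The plan gives no numerical result for the QALY analysis, so there is no figure to reproduce.

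**Inputs from the protocol article.** Sample size (14) says "the trial will require 37 patients in each group" and plans 84 recruited, so 84 / 2 = 42 per arm before losses. The discount rate is 5%. Eligible ages run from 18 to 75 years.

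**Assumptions (not in the document).** EQ-5D-5L index SD 0.15 to 0.25, equal at both times; slope beta of the 1-year value on baseline 0.3 to 0.7; remaining life L of 20 to 30 years. With equal SDs, beta equals the correlation rho.

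**Step 1: size of a chance baseline imbalance.** SE = SD × √(2/n).
- n = 37, SD 0.20: 0.20 × √(2/37) = 0.0465 (95% range about ±0.09).
- n = 37, SD 0.15 and 0.25: 0.0349 and 0.0581.
- n = 42, SD 0.20: 0.0436.

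**Step 2: share passed on by the change score.** With no true difference and an imbalance d, the expected difference in change is −(1 − beta) × d, in favour of the arm that started lower. For d equal to one SE and n = 37:
- Central: (1 − 0.5) × 0.0465 = 0.023.
- Lowest: (1 − 0.7) × 0.0349 = 0.0105.
- Highest: (1 − 0.3) × 0.0581 = 0.0407.

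**Step 3: lifetime factor.** (1 − 1.05^−L) / 0.05 = 12.46, 14.09 and 15.37 for L = 20, 25 and 30.

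**Step 4: spurious lifetime QALYs per patient for a one-SE imbalance.**

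| Case | n = 37 per arm | n = 42 per arm |
|---|---|---|
| SD 0.15, beta 0.7, L 20 | 0.13 | 0.12 |
| SD 0.20, beta 0.5, L 25 | 0.33 | 0.31 |
| SD 0.25, beta 0.3, L 30 | 0.63 | 0.59 |

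An imbalance of at least one SE, in either direction, occurs in about a third of trials.

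**Step 5: precision.** Variance of the change-score contrast over the adjusted contrast = 2(1 − rho) / (1 − rho²) = 2 / (1 + rho). The SE ratio is the square root.

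| rho | 0.2 | 0.3 | 0.5 | 0.7 |
|---|---|---|---|---|
| SE ratio | 1.29 | 1.24 | 1.15 | 1.08 |

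The share of information lost is 1 − (1 + rho)/2: 40% at rho 0.2 and 15% at rho 0.7.

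**Step 6: simulation check.** 20,000 trials, 37 per arm, SD 0.20, rho 0.5, no true effect. The mean contrast was about 0 for both methods. The SD of the contrast was 0.046 for change and 0.040 adjusted. The slope of the contrast on the imbalance was −0.50 for change and 0.00 adjusted. Among trials with an imbalance near +0.05, change gave −0.027 and the adjusted model −0.002.

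**Step 7: effect on the arm ratios (illustration).** Assume a true gain of 0.15 and equal costs in both arms. Splitting a spurious 0.023 evenly gives gains of 0.1385 and 0.1615. Cost per QALY then differs by 0.1615 / 0.1385 − 1 = about 17% between identical procedures.

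**The case against.** The strongest defence is that the paragraph never calls the change unadjusted and names no estimator for comparing arms. Defining QALYs through a change does not rule out adjustment: regressing the change on group and baseline gives the same group coefficient as regressing the 1-year value on group and baseline. The general model in 20a could also supply adjusted means for each arm, and an article may leave such detail to a fuller plan. This shows that the remedy is compatible with the text. It does not show that the text applies it. The article writes out a formula, ending in a division by each arm's change, and that formula has no step for a covariate.

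Other parts of the defence stand and limit the point:

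- A reader might infer that the QALY comparison is biased. It is unbiased over repeated randomisation. The error is conditional on the imbalance that occurs, and only the share (1 − beta) of it is carried over.
- A reader might infer that the lifetime projection makes matters worse. It scales true effect and error alike, so it enlarges the absolute figure but leaves the signal-to-noise ratio unchanged.
- A reader might blame the allocation scheme: "Patients will be allocated to one of the two treatment groups in a 1:1 ratio using permuted block randomization with variable block size", with no stratification factor named. That is largely beside the point. Stratifying by site, for instance, would not by itself balance EQ-5D-5L; the small sample is the reason to expect imbalance.
- The size rests wholly on assumed values for SD, slope and remaining life.

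**Conclusion.** The point holds as an avoidable weakness in a stated analysis rule. Followed literally, the cost-utility paragraph uses a less efficient estimate than the trial's own model offers, and one that is sensitive to chance baseline differences. Under the assumptions above, a one-SE imbalance is worth roughly 0.1 to 0.6 lifetime QALYs per patient, and the SE is about 8% to 29% larger than it need be across correlations of 0.7 to 0.2.

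Two stronger readings are not supported. First, a reader might conclude that the economic hypothesis depends on this figure. The hypothesis in the Abstract and Background is non-inferiority with lower expenses. Non-inferiority is judged on PRWE and expenses on costs, and neither uses the QALY difference. Second, a reader might conclude that the trial will report two conflicting EQ-5D-5L treatment effects. The cost-utility paragraph describes cost-per-QALY ratios for each arm; the EQ-5D-5L treatment effect is the marginal effect from the model in 20a. The two sections handle baseline differently, but they do not contradict each other.

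**What to change.** In Methods for additional analyses (20b), state that each arm's 1-year EQ-5D-5L change is the baseline-adjusted marginal mean at 1 year, evaluated at the pooled baseline mean, minus that pooled mean. It can come from the model in 20a, or from a regression of patient-level QALYs on group with baseline EQ-5D-5L as covariate, with arm means again taken at the pooled baseline. Use these adjusted quantities in the 1-year and lifetime QALY figures and in the arm-specific cost-per-QALY ratios. If an incremental ratio is reported, its denominator should be the adjusted between-group QALY difference; that difference should not be put directly into the arm-specific ratios.

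The cost is a short addition to the analysis text. Baseline EQ-5D-5L is already required for the change and for the planned model, so no further data or patients are needed.

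### The QALY rule uses only the 12-month EQ-5D-5L change, so the first-year recovery path does not enter the QALY term

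*Protocol article*

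**What the plan says.** The section Methods for additional analyses {20b} fixes the QALY calculation. For the trial period, "the change in this index at 1 year after surgery will be multiplied by the number of years spent in that health state". For the lifetime figure, "we will multiply the change in EQ-5D-5L index with the expected life years remaining", and "We will use a constant discount rate of 5% when calculating the total QALYs gained over lifetime". The cost ratio uses the same quantity: "we will divide the total expenses of FCA and PRC with the change of EQ-5D-5L". None of these steps contains an interim EQ-5D-5L value, and none says when the counted years begin.

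Three other parts of the article bear on this:

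- **Participant timeline:** "Follow-up will take place at 3 and 6 weeks, at 3, 6, and 12 months, and at 5 and 10 years post-treatment".
- **Rehabilitation:** the splint fitted in theatre stays on for 3 weeks. Then, "A short arm removeable splint will be used until 6 weeks after the procedure". Use of the hand as tolerated starts only from 6 weeks. This programme is the same in both arms for 12 weeks.
- **Background and rationale {6a}:** convalescence time is named, with adverse events and postoperative pain, among the considerations the trial should examine.

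On the cost side, the section EQ-5D-5L and cost-utility analysis includes the costs of complications and sick leave.

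**The concern.** A QALY is utility accumulated over time. The stated rule takes the level reached at 12 months and treats it as a flat gain. The article's own splinting schedule makes it unlikely that patients are in their 12-month state during the first weeks, so the flat gain does not describe year one, the part of the horizon that the trial observes most closely.

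The comparison between arms is also affected. The article expects similar clinical outcomes and doubts that superiority of either procedure can be shown. If the 12-month EQ-5D-5L changes turn out alike, any first-year QALY difference lies in the path to month 12, and the rule sets that difference to zero by construction. A loss of health from pain or a complication that has resolved by month 12 would appear among the costs but not among the QALYs. Lower economic expense is part of the trial's hypothesis, so the cost-utility analysis matters to its conclusions.

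**Working it through.** The article states no QALY figure, so there is nothing to reproduce. The check compares the rule with the trapezoidal area under the curve.

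**Inputs from the article:** the rule; visits at 3 and 6 weeks and at 3, 6 and 12 months; a 5% discount rate.

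**Assumed:** a 12-month change D of 0.15 (range 0.05 to 0.20) and the recovery paths below.

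**Step 1, the rule.** First-year QALY = D × T. If the years run from surgery, T = 1 and the result is 0.150. If they run from month 12, T = 0 and the result is 0.

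**Step 2, the area.** With u the change from baseline at times 0, 3/52, 6/52, 0.25, 0.5 and 1 year, the area is Σ (t₍ᵢ₊₁₎ − tᵢ)(uᵢ + u₍ᵢ₊₁₎)/2. This gives the six time points weights of 0.029, 0.058, 0.096, 0.192, 0.375 and 0.250, which sum to 1. Paths are written as shares of D, so the ratios do not depend on D.

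| Path (baseline, 3 wk, 6 wk, 3 mo, 6 mo, 12 mo) | Area ÷ D | Rule (T = 1) ÷ area | QALY at D = 0.15 |
|---|---|---|---|
| Full benefit at once | 1.000 | 1.0 | 0.150 |
| Plateau by 3 months (0, 0.3, 0.6, 1, 1, 1) | 0.892 | 1.1 | 0.134 |
| Gradual, no dip (0, 0, 0.2, 0.5, 0.8, 1) | 0.665 | 1.5 | 0.100 |
| Straight line | 0.500 | 2.0 | 0.075 |
| Dip, then gradual (0, −1, −0.5, 0.3, 0.7, 1) | 0.464 | 2.2 | 0.070 |
| Early overshoot (0, 0.8, 1.2, 1.6, 1.5, 1) | 1.282 | 0.8 | 0.192 |

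For straight-line recovery, the excess over the range of D runs from 0.5 × 0.05 = 0.025 to 0.5 × 0.20 = 0.100 QALY.

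A deeper dip, with assumed utilities 0.65, 0.45, 0.55, 0.65, 0.72 and 0.80, gives an area of 0.043 against 0.150, a ratio of 3.5. That path needs a fall of 0.20 below baseline at 3 weeks. A mild dip (0.65, 0.60, 0.65, 0.72, 0.78, 0.80) gives 0.097, a ratio of 1.5.

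**Step 3, equal 12-month change, different path.** With D = 0.15 in both arms, one on a plateau by 3 months and one with a dip and gradual recovery, the area difference is 0.15 × (0.892 − 0.464) = 0.064 QALY. If instead one arm is 0.05 better at the four interim visits and equal at 12 months, it is 0.05 × (0.058 + 0.096 + 0.192 + 0.375) = 0.036 QALY. The rule gives 0 in both cases, whichever start date is used.

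**Step 4, lifetime total.** With years counted from surgery and discounted at 5% from the start of each year, the factor Σ 1.05⁻ᵏ (k = 0 to L − 1) is 8.11 for L = 10 and 16.14 for L = 30. For straight-line recovery the first-year excess is 0.5 D, so its share of the total is 0.5/8.11 = 6.2% at 10 years and 0.5/16.14 = 3.1% at 30 years. For the dip-then-gradual path the shares are 6.6% and 3.3%.

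**The case against.** The strongest case on the other side has five parts.

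- **Direction.** A reader might infer that first-year QALYs are certainly overstated. The text does not establish this. It does not say that the years begin at surgery, and counting from month 12 would credit nothing for year one, an understatement on every gradual path above. Even from surgery, overstatement needs a positive gain reached gradually; an early overshoot reverses it. This objection stands, so the direction is conditional.
- **Size.** The article gives no utilities and no recovery curve. The 3.5-fold ratio rests on a deep assumed dip and should not be read as the expected error. The between-arm figures of 0.036 and 0.064 QALY also rest on assumed differences, and the identical 12-week rehabilitation gives no reason to expect a particular one. This stands.
- **Weight given to recovery.** A reader might infer that convalescence has no weight in the economic evaluation. That is not so: complications and sick leave are costed, and the repeated-measures model for continuous outcomes includes a group-by-time term. The zero applies to the QALY term alone.
- **Reach.** The lifetime effect per arm is a few per cent, and the primary PRWE comparison is untouched. This stands.
- **Data.** Table 4 is not shown, and the Outcomes section lists EQ-5D-5L among outcomes at the 1-year follow-up. The repeated-measures model suggests interim recording but does not prove it. A remedy without new data therefore cannot be promised in full.

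None of this changes the fact that a definite formula is stated and the first-year path does not enter it.

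**Conclusion.** The point holds in a conditional form. As written, the rule leaves the first-year path out of the QALY term under either reading of when the years start. Counted from surgery, it overstates first-year QALYs for a positive gain reached gradually, by 2-fold for straight-line recovery and roughly 1.1- to 2.2-fold over the gradual paths in the table. Counted from month 12, it credits year one with nothing. Two arms with equal 12-month change always show a zero first-year QALY difference.

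The ratios rest on assumed paths and the QALY amounts on an assumed change as well. The zero between-arm difference follows from the formula and needs no such assumption. The consequence is confined to the cost-utility analysis. It is material for the first-year QALY and the first-year comparison, and small for each arm's lifetime total.

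**What to change.** In Methods for additional analyses {20b}, replace the year-one rule with the trapezoidal area under the EQ-5D-5L curve, from baseline through every visit up to 12 months at which it is recorded. State that any projection beyond the trial year starts at month 12 from the 12-month level, which also settles when the counted years begin.

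If EQ-5D-5L is recorded only at baseline and 12 months, use the straight line between them. This gives half the 12-month change for every patient, so it corrects the level only: two arms with equal change still show no difference. The report should then state that differences in recovery path are not captured in the QALYs.

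The cost is a change of wording and a few lines of code. No new data are needed if interim values are already collected or if the straight line is accepted. If they are not collected and the path is wanted, EQ-5D-5L would have to be added to the interim visits. As the first participant was randomised in October 2020, those already past these visits would lack the values. The change is best made before the economic data are analysed. If recovery is gradual and the years were to be counted from surgery, the reported first-year gain will be smaller.
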